**Data selection criteria for Analysis:**

Unless otherwise stated, for baseline we have to use ASHA screening (ASHA screening 1 and ASHA follow-up 1) data. At post intervention we have to use Post intervention data collected by study interviewers linked with patient ID of ASHA screen positive data.

For certain tables the information at baseline may not be collected by ASHA during their screening. For all such instance, Baseline data collected by study interviewers will be used linked with patient ID of ASHA screen positive data.

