**Smart mental health Visit schedule and analysis for visit:**

The study will be reported in mainly 2 category:-

1. Baseline (As applicable, this will includes ASHA screening data available in in ASHA Screening 1 and ASHA follow up 1. OR Baseline data collected by study interviewers)
2. Post Intervention (collected by study interviewers)

All the subject at post intervention are screen positive subjects. They were screened positive either at Baseline by study interviewers or at Intervention visits (ASHA screening 1 and ASHA follow-up 1) by ASHA. All the screen positive subjects were followed by ASHAs which is available in the ASHA follow up data.

Unless otherwise stated, the summary tables will be presented under 2 category:-

1. Baseline
2. Post Intervention

The difference between Baseline and Post Intervention will provide effect of intervention.

Apart from the Post Intervention data, post stigma data was also collected. At the time of creating derived data for post Intervention, both data (Post Intervention and post stigma) are appended together and created a single data set. A flag variable containing record ("Post Intervention" & "post stigma") was created was created in derived data set to identify such records.

Unless otherwise stated, all the analysis will be presented for all the subject who are screen positive by ASHA.

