#### **Secondary Analysis Depression and Anxiety Score:**

The subjects are classified as screen positive if he/she fulfil either one of below mentioned three category:-

1. Depression Sore  $\geq 10$
2. Anxiety Score  $\geq 10$
3. Suicidal tendency Score  $\geq 1$

The depression and anxiety will be categorized as Normal if their total score is in between 0-

4. The score in between 5-9 will be classify as Mild. The score in between 10-14 will be classify as moderated. The score of 15 or greater will be treated as severe.

The Anxiety and Depression score will be categorized by their severity. The count and percentage for depression and Anxiety at baseline and post baseline will be presented by severity. A separate table will be presented for depression score  $\geq 10$  and anxiety score  $\geq 10$  at baseline and post intervention.

A separated table will be provides for the only screen positive subjects with the count and percentage of the symptoms which lead them to be screen positive.

The summary statistics (N, Mean, STD, Min and Max) for anxiety and depression score by visit will be presented. The difference in score between baseline and post intervention will be summarized in similar fashion. The mean difference in score between baseline and post intervention will be statistically analyzed by paired t-test. The p-value from the analysis will be presented in same table.

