|             | Difference        | xxxxx             | xx.xx (x.xxx) | xx.xx  | xx.x, xx.x | 0.xxx   | xxxxx                | xx.xx (x.xxx) | xx.xx  | xx.x, xx.x | 0.xxx   |

Table 8b: Change in Depression/Anxiety Score from Baseline to Post Intervention for those who had a score  $\geq 10$  at the beginning of the intervention as screened by ASHAs

| Visit             | -----Anxiety----- |               |        |            |         | -----Depression----- |               |        |            |         |
|-------------------|-------------------|---------------|--------|------------|---------|----------------------|---------------|--------|------------|---------|
|                   | N                 | Mean (SD)     | Midian | Min, Max   | P-value | N                    | Mean (SD)     | Midian | Min, Max   | P-value |
| Baseline          | xxxxx             | xx.xx (x.xxx) | xx.xx  | xx.x, xx.x |         | xxxxx                | xx.xx (x.xxx) | xx.xx  | xx.x, xx.x |         |
| Post Intervention | xxxxx             | xx.xx (x.xxx) | xx.xx  | xx.x, xx.x |         | xxxxx                | xx.xx (x.xxx) | xx.xx  | xx.x, xx.x |         |
| Difference        | xxxxx             | xx.xx (x.xxx) | xx.xx  | xx.x, xx.x | 0.xxxx  | xxxxx                | xx.xx (x.xxx) | xx.xx  | xx.x, xx.x | 0.xxxx  |

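### The default baseline is the score on which subjects were selected, may come from a visit named follow-up, and has no rule for which record counts when a subject has two

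*SAP*

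**What the plan says.** Only the SAP is at hand. Four of its statements bear on the point.

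- **Source of the baseline.** Under Data selection criteria for Analysis, the default is that "for baseline we have to use ASHA screening (ASHA screening 1 and ASHA follow-up 1) data". The visit schedule section agrees: baseline, as applicable, "this will includes ASHA screening data available in in ASHA Screening 1 and ASHA follow up 1", with interviewer-collected baseline as the alternative.
- **Nature of those visits.** The visit schedule section says subjects were found positive either at baseline by study interviewers or "at Intervention visits (ASHA screening 1 and ASHA follow-up 1) by ASHA".
- **Population and selection.** By default, "all the analysis will be presented for all the subject who are screen positive by ASHA". The section on depression and anxiety scores makes a subject positive on any one of a depression score of 10 or more, an anxiety score of 10 or more, or a suicide score of 1 or more.
- **Use of the difference.** "The difference between Baseline and Post Intervention will provide effect of intervention". For the scores, "The mean difference in score between baseline and post intervention will be statistically analyzed by paired t-test". The title of Table 8b places the starting score "at the beginning of the intervention as screened by ASHAs".

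No section says which record is the baseline value when a subject has both ASHA screening 1 and ASHA follow-up 1.

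**The concern.** A paired t-test needs one baseline value per subject. The SAP names two sources and gives no order of precedence, so two programmers could derive different data sets from the same text. The primary objective names the change in anxiety and depression scores, and the case control analysis also takes its starting value from ASHA screen data.

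Two features make the choice more than clerical. The ASHA score that serves as baseline is also the score that put most subjects into the analysis, so part of any fall is regression to the mean, and how large a part depends on which record is used. One of the two records also comes from a visit named follow-up. If some improvement had occurred by then, a baseline taken there would hide it. The first feature generally inflates the reported fall and the second shrinks it.

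**Working it through.** The SAP states no mean, SD, reliability or expected change, so there is no figure to reproduce. The following is illustrative.

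**Inputs.** From the SAP: cut-off 10, selection at either ASHA visit, post-intervention score by interviewer. Assumed: normal scores with mean 3 and SD 4; reliability r (correlation between any two measurements) from 0.6 to 0.9; independent errors; no true change. Entry through the suicide score is ignored.

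**One screen.** Standardised cut-off a = (10 − 3)/4 = 1.75. Normal density at a = 0.0863, upper tail = 0.0401, ratio 2.154. Spurious fall = (1 − r) × 4 × 2.154, which is 0.4 × 8.615 = 3.45 at r = 0.6 and 0.1 × 8.615 = 0.86 at r = 0.9.

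**Two screens.** Simulation of 4 million subjects per setting. Each is scored at screening 1, follow-up 1, interviewer baseline and post-intervention, and is selected if either ASHA score is 10 or more. Entries are mean baseline minus post; a negative value is a rise.

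| Baseline used | r=0.6 | r=0.7 | r=0.8 | r=0.9 |
|---|---|---|---|---|
| Screening 1, positives at screening 1 only | 3.45 | 2.58 | 1.72 | 0.86 |
| All positives, first qualifying score | 3.64 | 2.81 | 1.94 | 1.03 |
| Extra fall from admitting follow-up 1 positives | 0.19 | 0.22 | 0.22 | 0.17 |
| All positives, higher score | 3.78 | 2.98 | 2.16 | 1.29 |
| All positives, later score | 1.62 | 1.21 | 0.81 | 0.41 |
| First positive at follow-up 1, follow-up 1 score | 3.92 | 3.16 | 2.36 | 1.49 |
| First positive at follow-up 1, screening 1 score | −0.92 | −0.94 | −0.93 | −0.79 |
| All ASHA positives, interviewer baseline | 0.00 | 0.00 | −0.01 | 0.00 |

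Subjects first positive at follow-up 1 make up 41.5%, 38.7%, 34.5% and 27.5% of positives across the four settings.

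**Reading the table.** Most of the spurious fall is already present with one screen. Pooling on the first qualifying score adds about 0.2 points. The higher-score rule gives a fall 2.3 times (3.78/1.62) to 3.1 times (1.29/0.41) that of the later-score rule, for the same subjects and no effect.

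**The opposite direction.** If a share f of baselines comes from follow-up 1 and a share g of the true effect is present by then, the estimate keeps 1 − f × g of it: 1 − 0.10 × 0.25 = 0.975, down to 1 − 0.50 × 1 = 0.50. The SAP gives neither f nor g.

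**The case against.** A reader might infer that follow-up 1 scores are known to be post-exposure and screening 1 scores are clean. The SAP does not support that. Its intervention-visit label covers both visits, and it gives no exposure dates. If the label disqualifies follow-up 1, it disqualifies screening 1 too. What separates them is the name follow-up and the wording of Table 8b's title, which is weaker evidence.

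A reader might also infer that the same people were scored twice. The SAP does not say so. It states that positives were followed by ASHAs in the follow-up data, but not whether follow-up 1 belongs to those data. If follow-up 1 covered only earlier negatives, no one already positive could have a diluted baseline. If it covered only people missed at screening 1, the second chance of selection disappears as well.

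The model can be criticised too. A normal distribution with mean 3 and SD 4 puts 23% of scores below zero, while the SAP's lowest category starts at 0, and subjects who enter on the suicide score need not regress. Table 8a already has an interviewer block, though it is not stated to cover the ASHA-positive IDs.

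These objections stand as limits on size and direction. They do not supply the missing record rule, and they do not alter the fact that the baseline is the selecting score.

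**Conclusion.** The defect is a baseline that is the selecting score, may come from a visit named follow-up, and is not uniquely defined. The SAP then reads the change from it as the intervention effect.

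Under the assumed inputs, the record rule alone moves the null result between 0.4 to 1.6 points (later score) and 1.3 to 3.8 points (higher score), if everyone has both records. The part due to admitting follow-up 1 positives on their first qualifying score is only about 0.2 points. It would be wrong to charge pooling with the whole fall of 1.5 to 3.9 points among those subjects, because selecting on 10 or more at screening 1 alone already gives 0.9 to 3.4 points. Dilution from follow-up 1 is possible but cannot be sized, so no net direction of bias can be claimed.

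Table 15 is outside the point. Its baseline is a treatment-history question, not a score selected by threshold.

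**What to change.** 1. **One record per subject.** In Data selection criteria for Analysis, set the baseline to the ASHA screening 1 score for subjects positive at screening 1, never replaced by a follow-up 1 score. State what follow-up 1 was and who was scored there.
2. **Separate row.** Show subjects first positive at follow-up 1 in a descriptive row. Do not test a change from their screening 1 score: it was selected to be below threshold, and in the model it gives a spurious rise of 0.8 to 0.9 points.
3. **Sensitivity analysis.** Repeat Tables 8a and 8b, and the cases of Table 16a, with the interviewer-collected baseline for the same ASHA-positive patient IDs. The SAP already provides for this linkage where ASHAs did not collect an item. The ASHA did not select these subjects on that score, and its null change is about 0 in the model if interviewer and ASHA errors are independent. For Tables 8b and 16a, keep the condition of 10 or more on the ASHA score. Re-applying it to the interviewer score among all ASHA positives brings back a null fall of 2.4, 1.8, 1.1 and 0.6 points at r = 0.6, 0.7, 0.8 and 0.9 (same simulation). Limit this to the cases in Table 16a, because the controls are defined by a positive interviewer screen.

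Step 1 does not remove regression to the mean from screening 1, which is why step 3 is needed. The cost is SAP wording, one derivation rule and a few extra table rows, with no new data. The downside is fewer subjects in the main row, a sensitivity analysis limited to those with a linked interviewer baseline, and probably a smaller reported fall.

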**Smart mental health Final Statistical Analysis plan Primary Analysis:**

The primary objective of the study is:-

To see the difference in anxiety and depression score and health service utilization among the mental health screen positive subject post intervention.

The screen positive subjects at baseline will be looked for their past history for mental health service utilization. The subjects who responded "Yes" against question number 56 "Did you get treated for that mental disorder?" are proportion of subject at baseline who used mental health service.

At post intervention, the number of subjects used health service can be taken from Doctors follow-up data.

The count and percentage will be provided for the subjects who are screen positive for utilization of health services. Proportion of mental health service utilization at baseline and post intervention among the screen positive subject will be statistically analyze by McNemar test. The P-value for comparison of will be presented in same table.

A separate table will be provided for subjects screen positive subjects who actually visited doctor for their treatment at time of intervention. The count and percent by visit will be provided for this.

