|------------------------------------------------------------------------------------|-----------------------------|
| Have you ever been told by a health provider that you have heart attack or angina? | (xx.xx) xxx                 |
| Have you ever been told by a doctor that you have or had Stroke?                   | (xx.xx) xxx                 |
| Have you ever been told by a doctor that you have or have had Diabetes?            | (xx.xx) xxx                 |
| Have you ever been told by a doctor that you have or have had Cancer?              | (xx.xx) xxx                 |
| Have you ever been diagnosed to have any mental disorder?                          | (xx.xx) xxx                 |
| Did you get treated for that mental disorder?                                      | (xx.xx) xxx                 |

*N=Total no. of patients in Baseline; n=No. of patients in particular category*

*Percentages for (Did you get treated for that mental disorder? ) Is calculated on number of patients diagnosed for mental disorder.*

Table 14a: Summary of treatment History among ASHA screened positive Patients

| Question                                                               | Baseline(N=xxxx)
n(%) |
|------------------------------------------------------------------------|--------------------------|
| Are you currently taking any western medicines regularly?              | xx(xx.xx)                |
| Are you currently taking any medicines for mental disorders regularly? | xx(xx.xx)                |

*N=Total no. of patients in Baseline; n=No. of patients in particular category*

Table 14b: Summary of treatment History during intervention among ASHA screened positive Patients

| Question                                                                              | Baseline(N=xxxx)
n(%) |
|---------------------------------------------------------------------------------------|--------------------------|
| Did you get treated for your mental health condition as indicated by ASHA/Interviewer | xx(xx.xx)                |

*N=Total no. of patients in Baseline; n=No. of patients in particular category*

Table 14c: Summary of treatment compliance among treated patients of ASHA screened positive

| Question                                                                            | Baseline(N=xxxx)
n(%) |
|-------------------------------------------------------------------------------------|--------------------------|

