| Did you take medicines as prescribed by the primary care doctor on a regular basis? | xx(xx.xx)                |

*N=Total no. of patients in Baseline; n=No. of patients in particular category*

Table 15: Summary of for Utilization of Health Services for Screen Positive subjects

| Screen Positive | Health Service used ** | Baseline
(N=xxxxx)
n (%) | Post Intervention
(N=xxxxx)
n (%) | P-value |
|-----------------|------------------------|--------------------------------|-----------------------------------------|---------|
| By ASHA         | Yes                    | xxx (xx.xx)                    | xxx (xx.xx)                             | 0.xxxx  |
|                 | No                     | xxx (xx.xx)                    | xxx (xx.xx)                             |         |
| By Interviewer* | No                     | xxx (xx.xx)                    | xxx (xx.xx)                             | 0.xxxx  |
|                 | Yes                    | xxx (xx.xx)                    | xxx (xx.xx)                             |         |

\* This includes only those patients who were screen positive by Study Interviewer but not by ASHA.

\*\* Health Service used: At baseline: Response from the question "Did you get treated for that mental disorder?"

At Post Intervention: Response from the question "Did you get treated for your mental health condition as indicated by ASHA/Interviewer?"

P-Value is calculated based on Mc-nimar test for matched pair test of proportion.

Table 16a: Case control analysis of Change in Depression/Anxiety Score from Baseline to Post Intervention for those who had a score  $\geq 10$  at the beginning of the intervention.

| Category   | Type    | Statistics | Baseline     | Post Intervention | Change       | P-Value for difference |
|------------|---------|------------|--------------|-------------------|--------------|------------------------|
| Anxiety    | Cases   | N          | xxxxx        | xxxxx             | xxxxx        | 0.xxxx                 |
|            |         | Mean (SD)  | xx.x (xx.xx) | xx.x (xx.xx)      | xx.x (xx.xx) |                        |
|            |         | Median     | xx.x         | xx.x              | xx.x         |                        |
|            |         | Min, Max   | xx; xx       | xx; xx            | xx; xx       |                        |
|            | Control | N          | xxxxx        | xxxxx             | xxxxx        |                        |

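### The primary before-after test of service use pairs two different treatment questions, so its p-value does not measure change in use, and the SAP names two sources for the post value.

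*SAP*

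**What the plan says.** The primary objective is "To see the difference in anxiety and depression score and health service utilization among the mental health screen positive subject post intervention". Service use is therefore one of its components.

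- **Baseline value (Primary Analysis).** The text says "The screen positive subjects at baseline will be looked for their past history for mental health service utilization" and counts as users those who answered Yes to question 56, on whether they were treated for that mental disorder.
- **Where the baseline item sits (Table 13).** It follows "Have you ever been diagnosed to have any mental disorder". The footnote says that its percentage "Is calculated on number of patients diagnosed for mental disorder".
- **Post value, text (Primary Analysis).** "At post intervention, the number of subjects used health service can be taken from Doctors follow-up data".
- **Post value, tables (footnotes of Tables 15 and 16b).** The answer to "Did you get treated for your mental health condition as indicated by ASHA/Interviewer". The same item appears in Table 14b, whose title places it during the intervention.
- **Test.** "Proportion of mental health service utilization at baseline and post intervention among the screen positive subject will be statistically analyze by McNemar test". The Table 15 footnote repeats this as a matched-pair test.
- **Reading.** The visit schedule section says that the baseline-to-post difference gives the effect of the intervention.
- **Default source.** The data selection section takes post values from interviewer-collected data unless otherwise stated.

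**The concern.** A McNemar test compares two paired Yes rates. The comparison describes change only if Yes means the same thing on both occasions. Here the two items appear to differ in the condition asked about, in who can meaningfully answer, and in the period covered. A subject treated years ago and not since would count as a decline. A subject never diagnosed before could only stay the same or move upward. The SAP nevertheless intends the difference to be read as the effect of the intervention on a primary outcome.

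Separately, two post sources with no rule of precedence leave the analyst free to choose between them after seeing the data.

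**Working it through.** **1. The SAP's own figure.** There is none to reproduce. The SAP gives no sample size, significance level, expected rate or discordant proportion for this test. The check is a comparison of sections, followed by an illustration on assumed inputs.

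**2. The paired items side by side.**

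| | Baseline item (question 56) | Post item (Tables 15, 16b) |
|---|---|---|
| Condition | The disorder in the preceding item on ever having been diagnosed | The condition indicated by ASHA or interviewer |
| Who it applies to | Diagnosed patients, by the Table 13 denominator | All screen-positive subjects |
| Period | Past history, no stated window | During the intervention (Table 14b title) |

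The items agree on none of the three rows. If the doctors' follow-up data were used for the post value instead, the pair would still not match.

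**3. The post source.** The Primary Analysis text names doctors' follow-up data. The footnotes of Tables 15 and 16b name the question response, which agrees with the default in the data selection section. That default yields where something else is stated, and the Primary Analysis text does state something else.

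**4. The denominator.** Table 13 takes question 56 on diagnosed patients, while Table 15 shows all screen positives. The SAP does not say whether never-diagnosed subjects count as No or as missing. With assumed counts of 500 screen positives, 40 diagnosed and 20 Yes, the baseline rate is 20/40 = 50% on one base and 20/500 = 4% on the other. If never-diagnosed subjects were missing, only 40 of 500 pairs would remain.

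**5. Illustration of the mismatch (all inputs assumed).** Let b and q be the Yes rates of the two items, independent within subject, differing only because the items ask different things. Then p10 = b(1−q), p01 = q(1−b), d = p01 − p10 and s = p01 + p10. For a two-sided 0.05 test, the rejection probability is approximately Φ[(|d|√N − 1.96√s)/√(s − d²)], the opposite tail being negligible unless d is near zero.

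Worked case, b = 5%, q = 10%, N = 200: p10 = 0.045, p01 = 0.095, d = 0.05, s = 0.14. The argument is (0.7071 − 0.7334)/0.3708 = −0.071, so the probability is 47%.

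| b v q | N=200 | N=500 | N=900 |
|---|---|---|---|
| 5% v 5% | 5% | 5% | 5% |
| 2% v 5% | 37% | 73% | 93% |
| 5% v 10% | 47% | 85% | 98% |
| 10% v 5% | 47% | 85% | 98% |

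The first row uses both tails. The last row would be an apparent fall in use. The test holds its level only if the two items happen to have equal Yes rates.

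**6. Illustration of the source choice (assumed).** Take N = 500 with 25 baseline Yes and about 2 subjects Yes on both items. If one source gives 40 post Yes, the discordant pairs are 23 v 38 and the exact p is 0.072. If the other gives 50, they are 23 v 48 and p is 0.004. Ten subjects change the conclusion at 0.05.

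**The case against.** - **McNemar is the standard test for paired binary data.** This stands. A reader might infer that the test itself is invalid here. It is not: it correctly tests equality of two paired Yes rates. The fault lies in the variables supplied and in the reading given to their difference.
- **The lifetime period and the restriction to diagnosed subjects are inferred.** This also stands. Question 56 states no window, and the questionnaire's skip rules are not shown. The inference rests on the wording of the preceding item, the description as past history, and the Table 13 denominator. The mismatch in condition does not depend on it.
- **The source conflict is narrow.** Largely fair. The doctors' follow-up sentence is permissive, and the visit schedule, the data selection rule and both footnotes point to interview data. It is still the endpoint definition in the primary analysis section, and it conflicts with them.
- **Bias against the controls.** A reader might infer that doctors' follow-up data would make ASHA-negative controls non-users by construction. The SAP does not support this. It does not say whom those data cover, its visit schedule section says that ASHAs followed all screen-positive subjects, and Table 16b uses the question response.
- **The illustrations use invented rates.** True. They show how the test behaves and are not estimates for this study.

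**Conclusion.** The point holds as an endpoint-definition fault in a primary analysis. The Table 15 p-value compares Yes rates on two different items, and reading their difference as the effect of the intervention is unsupported. The post value is also defined in two conflicting ways.

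A reader might infer that the test is biased towards showing a rise. The documents do not settle that. A restriction to diagnosed subjects would lower the baseline rate, while an open recall period would raise it. Neither the size nor the direction of the net distortion can be computed from the SAP.

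The conclusion assumes that question 56 refers back to the item listed just before it in Table 13. Table 16b lists the same two items and does not say to which visit its single chi-square p-value applies.

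**What to change.** 1. **One post source.** In the Primary Analysis section, replace the doctors' follow-up sentence with the interviewer question already named in Tables 15 and 16b. Keep doctors' data for the separate table of subjects who saw a doctor, and as a sensitivity analysis.
2. **No before-after p-value.** Delete the McNemar test from both the Primary Analysis text and Table 15, including its footnote. Show past treatment at baseline and treatment during the intervention as separate descriptive proportions with 95% CIs. State that their difference is not interpreted as an intervention effect.
3. **Coding.** State that never-diagnosed subjects count as No for past treatment. Optionally, report treatment during the intervention by past treatment (yes or no).
4. **Table 16b.** Restrict the case versus control chi-square test to the post item, which is the same question in both groups, and say so in the case control section.

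The cost is changes to SAP text and table shells, using data already planned. The sponsor loses a before-after p-value for service use.
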